### Interim analyses {21b}

N./a. We do not plan any interim analyses.

### Methods for additional analyses (e.g., subgroup analyses) {20b}

Subgroup analyses will be conducted to explore the differential effects of alpha-tACS and tDCS in specific patient subsets, such as by age, sex, type of surgery, or baseline cognitive function.

All subgroup analyses will be exploratory. According to the European Medicines Agency (EMA) Guideline on subgroup analyses in confirmatory trials (2019, January 31) and the NEJM publication on reporting of subgroup analyses the regression models with interaction terms of subgroups by treatment form the starting point of the subgroup analyses with separate models for each of the subgroup analyses [46]. Additionally, we will provide subgroup specific estimates with 95% CI based on these models using a forest plot to allow exploratory evaluation on the direction and magnitude of treatment effects in subgroups. Estimates derived from exploratory subgroup analyses should be interpreted with caution.

### Methods in analysis to handle protocol non-adherence and any statistical methods to handle missing data {20c}

To address missing data, we will employ a two-pronged approach. For missing values assumed to be Missing Completely at Random (MCAR) or Missing at Random (MAR), we will utilize Multiple Imputation by Chained Equations (MICE). This method iteratively imputes missing values based on the relationships between variables, resulting in 30 complete datasets for subsequent analyses. In cases where the reason for missingness is known (informed missingness), targeted single imputation techniques will be employed. The specific imputation strategy (worst-case or best-case scenario) will be chosen based on the nature of the missing data. This approach mitigates the effects of dropouts or deviations from the protocol.

### Plans to give access to the full protocol, participant-level data and statistical code {31c}

The contact of the corresponding author will be communicated allowing researchers to get in touch with the investigators. Data can be made available upon written request in conformance with the GDPR.

## Oversight and monitoring

### Composition of the coordinating center and trial steering committee {5d}

The trial is coordinated by a team composed of senior and junior neurologists, anesthesiologists, and psychologists. The principal investigators will oversee and train one junior physician from the department of anesthesiology and one junior physician from the department of neurology who will be running the trial day-by-day and either assist or oversee the intervention. A monthly meeting will take place to discuss the trial status as well as issues that occur.

### Composition of the data monitoring committee, its role and reporting structure {21a}

There will be no independent data monitoring committee due to the lack of external sponsors.

### Adverse event reporting and harms {22}

TES allows for painless modulation of cortical activity and excitability through the intact skull. Within the application parameters described above, tES is proven to be a well-tolerated technique with few, mild side effects. At the standard parameters of tES (intensity 2 mA), a meta-analysis described the primary undesirable side effects as itching (39%), tingling (22%), headaches (15%), burning (9%), and discomfort (10%) [47]. All side effects were mild and short-lived, with most symptoms showing no difference between active stimulation and sham stimulation [48]. Rarely, and only after hours of continuous use, mild headaches and skin irritation at the electrode sites occur, which completely subside after the end of use.

However, we will closely monitor adverse events during and after the intervention. Concretely, study staff will be continuously present during the intervention. A physician will always assist to the intervention in the PACU or be on call in-hospital. Due to the setting in the PACU, physicians are permanently present in the room in case of adverse effects occurring. After the intervention, patients will be asked about itching, pain, burning, feeling of warmth/heat, metallic iron taste, fatigue/reduced attention, or other symptoms.

All adverse events and serious adverse events will be documented and promptly reported, including details on expectedness, seriousness, severity, and causality, to the principal investigator, the Project Management Group, and the Trial Steering Group. The principal investigator will address all reported events as quickly as possible, and no later than within 24 h. This process complies with the EMA ICH E6 (R3) Guideline on Good Clinical Practice (GCP) (May 25, 2023). Significant concerns requiring a reassessment of expected risks will also be immediately communicated to the Ethics Committee of Greifswald University Hospital. These measures ensure the timely and transparent handling of safety concerns, prioritizing participant safety and well-being. For subsequent studies beyond this piloting and feasibility phase, we plan to establish an independent safety monitoring board to oversee the reporting and management of all adverse events.

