### Intervention description {11a}

Patients will be enrolled at least 1 day before surgery. Questionnaires regarding contraindications for tES as well as baseline questionnaires will be handed out (PPI, HADS, STAI, PCS, BRI, PSQ, DN4). The preoperative cognitive status will be assessed with a MoCA score.

On the day of the surgery, a 64-channel EEG will be recorded in the preoperative holding area. Preoperative delirium and pain will be assessed with standardized tests (RASS, 3D-CAM, and NRS). A preoperative blood sample will be drawn. Before induction of anesthesia, a frontal EEG recording will be started that will last until the end of anesthesia.

A single tES intervention will take place postoperatively in the PACU, after return of consciousness and patient handover to the PACU staff. Emergence of delirium in the PACU (PACU-D) will be assessed, and patients will be asked about postoperative nausea and vomiting (PONV) as well as pain using standardized tests (RASS, 3D-CAM, and NRS) every 30 min for 1 h in the post-anesthesia care unit (PACU). A 64-channel EEG will be recorded, and a second blood sample will be drawn after the tES intervention.

During the first 5 postoperative days, patients will be screened twice daily for POD and pain using standardized tests (RASS, 3D-CAM, and NRS). A third blood sample will be drawn on the second postoperative day (Fig. 1).

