**Fig. 2 Fig2:**
[figure not shown]
Illustration of electrode placement and electric field distribution. Applied transcranial electrical stimulation on an MNI head/brain for (**A**) tACS group (stimulation frequency: 9.5 Hz; electrodes centered over P3 and P4; electrode diameter: 5 cm) and (**B**) tDCS group (electrodes centered over F3, anode, and Fp2, cathode; electrode diameter: 5 cm), simulated using SimNibs [58, 59]. tACS transcranial alternating current stimulation, tDCS transcranial direct current stimulation

The sham group is divided into two subgroups with n(tDCS)/2 for tDCS-sham and n(tACS)/2 for tACS-sham. In these subgroups, the same electrode arrangements and ramp times are used, but the current is only applied for 30 s to induce the typical tingling sensation on the scalp and blind the patients to the stimulation condition.

The perception of side effects associated with the stimulation and group affiliation is surveyed at the end of each stimulation condition using a standardized questionnaire [27].

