**Postoperative assessments**						
	Arousal (RASS)		x		x	x
	POD (3D-CAM)		x		x	x
	Pain (NRS)		x		x	x

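### The post-stimulation question list does not name tingling, headache or discomfort, three of the five main side effects the protocol itself cites, so these may be under-ascertained

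*Protocol article*

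**What the plan says.** All references are to the protocol article.

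- *Adverse event reporting and harms {22}* lists the primary undesirable effects at the standard intensity of 2 mA: "itching (39%), tingling (22%), headaches (15%), burning (9%), and discomfort (10" (the last figure is 10%).
- The same section gives the question list: "After the intervention, patients will be asked about itching, pain, burning, feeling of warmth/heat, metallic iron taste, fatigue/reduced attention, or other symptoms".
- Between these two statements it says: "Rarely, and only after hours of continuous use, mild headaches and skin irritation at the electrode sites occur".
- The text under Figure 2 says that the perception of side effects, together with perceived group affiliation, "is surveyed at the end of each stimulation condition using a standardized questionnaire". The items of that questionnaire are not reproduced. The same text describes tingling as typical and uses the 30-second sham current to induce it.
- *Secondary outcome measures* lists adverse events, without an ascertainment method or time window.
- *Intervention description {11a}* says of the first five postoperative days: "patients will be screened twice daily for POD and pain using standardized tests (RASS, 3D-CAM, and NRS". It mentions no adverse-event question at these visits.

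**The concern.** A symptom that is asked for by name is generally reported more fully than one the patient has to bring up. Here the named items and the expected effects do not match. Tingling, the second most frequent effect cited, has no item of its own. Headache has only *pain*, and a patient just out of major surgery will usually have wound pain, so a positive answer does not identify headache. Discomfort has no item.

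Two results depend on this. One is the adverse-event secondary outcome, which will be read as a tolerability profile for tACS and tDCS in older surgical patients. The other is the check on blinding. The sham is designed to reproduce tingling, so whether active and sham patients report it equally often is direct evidence on whether the sham worked. The survey already asks about perceived group affiliation at the same moment, so leaving tingling to the open prompt loses information that would cost almost nothing to collect.

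**Working it through.** No sample size, power or alpha figure depends on this point. The check compares two lists in one section, then gives a sense of scale.

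**Step 1. Match the cited effects to the items asked** (both from *Adverse event reporting and harms {22}*).

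| Effect cited | Rate | Closest item asked |
|---|---|---|
| Itching | 39% | Itching |
| Tingling | 22% | Open prompt only |
| Headaches | 15% | *Pain*, with no site given |
| Burning | 9% | Burning |
| Discomfort | 10% | No specific item |

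Two of the five cited effects have a named item and three do not. Conversely, four of the six named items (pain, warmth, metallic taste, fatigue or reduced attention) have no direct counterpart among the five.

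**Step 2. Expected counts.** *Sample size {14}* gives 225 participants in three equal groups: 225 / 3 = 75 per group and 2 × 75 = 150 on active stimulation. Expected count = n × cited rate, assuming the cited rates hold for both active arms:

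- Tingling: 150 × 0.22 = 33 (75 × 0.22 = 16.5 per arm)
- Headache: 150 × 0.15 = 22.5 (75 × 0.15 = 11.25 per arm)
- Discomfort: 150 × 0.10 = 15 (75 × 0.10 = 7.5 per arm)

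These are patients expected to have the effect, not patients expected to be missed.

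**Step 3. How much might be lost.** The document gives no figure for how often an unnamed effect is still recorded, so the capture fraction *c* is an assumption. Observed rate = c × true rate.

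| Assumed c | Tingling, of 150 | Headache, of 150 | Discomfort, of 150 |
|---|---|---|---|
| 100% | 33.0 (22%) | 22.5 (15%) | 15.0 (10%) |
| 80% | 26.4 (17.6%) | 18.0 (12%) | 12.0 (8%) |
| 50% | 16.5 (11%) | 11.25 (7.5%) | 7.5 (5%) |
| 30% | 9.9 (6.6%) | 6.75 (4.5%) | 4.5 (3%) |

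If *c* is the same in every arm, the ratio of rates between arms is unchanged, but each absolute rate and each difference in rates shrinks by the factor *c*.

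**Step 4. The two headache statements.** One sentence gives headaches as a primary effect at 15% at 2 mA. Two sentences later, mild headaches are said to occur rarely and only after hours of continuous use. The session in this trial lasts 20 minutes at 2 mA. The first statement implies about 22 headaches among 150 patients and the second implies close to none. As printed, they cannot both describe this intervention.

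**The case against.** The strongest reply is that the instrument is not visible. The survey uses a cited standardized questionnaire, and the sentence in the harms section may only summarise it, so tingling and headache could well be on the form. The printed list also contains *pain*, which can take in headache, and ends with an open prompt. This stands. It rules out any claim that these effects will be missed, though if the form does name them, the printed list still needs correcting.

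A reader might go further and infer that events after the PACU go unrecorded, because the ward visits are described as RASS, 3D-CAM and NRS only and Table 1 has no adverse-event row. The document does not support that. The harms section commits to monitoring during and after the intervention and to documenting and reporting all adverse and serious adverse events. Table 1 is not exhaustive: it also lacks rows for nausea and vomiting and for the side-effect survey, both of which the text plainly describes. Visit-level prompts are the kind of detail a condensed article leaves to the full protocol or case report form. What remains is only that the article describes no systematic question on the ward.

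The timing of the survey is also defensible. The plan describes the effects as mild and short-lived, so asking straight after stimulation is sensible. Patients are stimulated only after return of consciousness and handover, so describing them all as too drowsy to answer would overstate matters. Finally, staff are blinded and the procedure is the same in all arms, so under-elicitation would not obviously favour one arm. The consequence is mainly for absolute rates.

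**Conclusion.** The printed question list does not name three of the five side effects that the same section ranks as primary. At the cited rates these would affect about 33 (tingling), 22 (headache) and 15 (discomfort) of 150 actively stimulated patients, and they may be under-ascertained in the adverse-event outcome. The counts assume that the cited rates apply to both active arms and that all 225 patients are enrolled and stimulated as planned. The extent of any loss is unknown, and the 30% to 100% capture range is purely illustrative.

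The conclusion that the outcome will under-count known risks, or that ward events escape recording, goes beyond the text. The two headache statements do conflict. That is background wording and changes no analysis step, but readers will use it to judge expected harms. Overall this is a modest point, worth acting on because the remedy is specific and nearly free.

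**What to change.** 1. Add tingling, headache (worded so that it is separate from surgical pain) and discomfort as named items to the existing post-stimulation survey, identically in all three arms. If the questionnaire already contains them, correct the list in *Adverse event reporting and harms {22}* to match it.
2. Reconcile the 15% headache figure with the sentence on hours of continuous use.
3. Optionally, add one open adverse-event question at the ward visits already made, or state how events after the PACU are found, since monitoring after the intervention is promised.
4. For patients surveyed before the change (28 of 225 had completed the trial by April 2024, per *Trial status*), record the new items as not asked rather than absent.

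Cost: three form items, no new visits, and somewhat more minor background complaints recorded in every arm. A further ward question would add a little time at each contact.

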### Frequency and plans for auditing trial conduct {23}

The trial will undergo regular audits to ensure compliance with the study protocol and regulatory standards. The Project Management Group will meet weekly, or more frequently if needed, to review progress, address issues related to data collection or the intervention, and implement necessary adjustments to study procedures. Quarterly meetings of the Trial Steering Group will oversee the trial’s overall objectives, ensuring participant safety and data integrity. The Ethics Committee of Greifswald University Hospital will be informed of trial progress and any significant developments, convening as necessary to review patient safety and protocol adherence. This structured oversight framework ensures rigorous monitoring and quality assurance throughout the trial.

### Plans for communicating important protocol amendments to relevant parties (e.g., trial participants, ethical committees) {25}

All protocol amendments will be communicated to the local ethics committee of the Greifswald University Hospital. The registry entry will be updated, as well as the published trial protocol.

## Dissemination plans {31a}

The results of the study will be published in peer-review journals in the interest of disseminating scientific knowledge, irrespective of the result. At the conclusion of the trial, a summary of the results will be prepared and shared with participants, as well as the nursing staff and healthcare professionals involved in patient care. Additionally, the results will be disseminated within the hospital through departmental meetings, allowing our colleagues to stay informed about the findings and potential implications for clinical practice. This approach ensures that all involved parties, including participants and healthcare staff, are informed and engaged with the study’s outcomes.

## Discussion

The aim of this trial is to assess the effectiveness of a single postoperative transcranial electrical stimulation (tES) session in the PACU to prevent postoperative delirium (POD) in elderly patients undergoing elective major surgery. Interventions will compare alpha-tACS (9.5 Hz, 2 mA peak-to-peak, 20 min) over the PPC and anodal tDCS (2 mA, 20 min) over the left DLPFC with sham.

With the MoDeSt trial, we address the growing need for safe treatment protocols for elderly patients when surgery in general anesthesia is necessary. The prevention of POD and postoperative pain by tES poses a potential way to alleviate a relevant burden a surgical intervention can impose on elderly patients. This may prove an essential approach to avoid the emergence of the long-term neurocognitive decline associated with POD, leading to severe consequences for individuals as well as profound socioeconomic impacts.

Research in the neuroanesthetic field has extensively shown the critical association between POD and pre- [49], intra- [11, 50], and postoperative [51–53] EEG power in the alpha band. Low intraoperative alpha power seems to reflect the EEG phenotype of a “vulnerable brain” [52–54]. Interventions modulating this neurophysiological characteristic were lacking. A promising approach is to maximize alpha power with intraoperative pharmacological manipulation [55]. In the alpha-tACS arm of this trial, we will investigate if the stimulation with a weak alternating current in the alpha frequency range during emergence of anesthesia modulates the neural network communication and thereby influences the postoperative neurocognitive outcome.

Our comprehensive outcome measures, including the incidence, phenotype, and severity of delirium, alongside complex neurophysiological and biofluid biomarker evaluations, will offer an in-depth insight into the impact of tES, but will also shed light upon the neurophysiological background of POD. Application of tES has been associated with reduced levels of inflammatory biomarkers (IL-6, IL-10, TNF-alpha, ß-endorphin, and BNDF) commonly linked with POD [56, 57], though the impact of postoperative tES on perioperative biomarker dynamics has yet to be examined. Developing predictive models based on perioperative clinical data and biomarkers will potentially identify patients who could most benefit from tES interventions. If effective, tES could become a simple, easy-to-use, and cost-efficient method to enhance neurocognitive recovery after general anesthesia.

Overall, the trial’s outcomes will explore the therapeutic potential of postoperative tES in elderly patients undergoing general anesthesia for major surgery and contribute to our understanding of the pathophysiological correlates of delirium.

## Trial status

This is the first version of the protocol, dated 02 April 2024. Recruitment began in February 2024 and is expected to be completed within 1 year. Up to date (April 2024), 28 patients completed the trial.

## Data Availability

The datasets will be made available from the corresponding author upon written reasonable request.

## Abbreviations

POD: Postoperative delirium
tES: Transcranial electrical stimulation
tDCS: Transcranial direct current stimulation
tACS: Transcranial alternating current stimulation
EEG: Electroencephalography
GDPR: General Data Protection Regulation
PONV: Postoperative nausea and vomiting
DLPFC: Dorsolateral prefrontal cortex
PPC: Posterior parietal cortex
